#### Exploratory Assessments

##### Multiday Boston Remote Assessment for Neurocognitive Health

We are exploring the feasibility of integrating daily mobile cognitive functioning assessments via the Boston Remote Assessment for Neurocognitive Health (BRANCH) platform [160,187,188]. The multiday paradigm using BRANCH can be self-administered without researcher supervision using any web-enabled device (mobile phone, tablet device, or computer). Similar to RBANS assessments, we provide an iPad for participants who do not own a web-enabled device to complete the multiday BRANCH tests. Participants complete 1 BRANCH test per day for 7 days during the 3 main assessment periods; they complete a unique version at each time point (before the intervention, after the intervention, and the 6-month follow-up). Participants complete a brief sequence of three visual associative memory tasks involving everyday objects: (1) Digit-Signs Test (correct number of street sign–number pairings identified), (2) Groceries Prices Test (correct number of grocery-price pairings identified), and (3) Face-Name Test (average of correct responses from 2 face-name pairings: first letter name recall and full name recall). Multiday learning curves to capture the speed and learning of BRANCH stimuli will be computed for each task [160]. Participants are instructed to take the multiday BRANCH tests in a quiet, distraction-free environment. Participants indicate a preferred time to complete the assessment once per day. They receive automated and secure SMS text messages or email reminders with a link to access the test. The administration of the multiday BRANCH tests takes approximately 12 minutes per day. The multiday BRANCH tests have demonstrated strong feasibility, reliability, validity, and sensitivity to subtle changes in learning and memory in preclinical AD/ADRD [160,189].

##### Daily Surveys

Participants receive daily surveys to indicate adherence and SCD symptoms during the intervention phase. Daily surveys are sent from Twilio (Twilio Inc), a messaging platform with REDCap integration. Participants can receive the surveys via telephone calls, SMS text messages, or secure email according to personal preference. Daily surveys for MHB participants include (1) logging mindfulness practice (*yes* or *no*), (2) program mindfulness skills practiced (all that apply), and (3) total time (in minutes) spent practicing these skills. Similar to other mindfulness RCTs [161], HEP participants are asked to report daily minutes spent journaling to control for the time and attention devoted to the active skills in MHB. Participants in both groups will provide a global rating of perceived SCD (*What is your level of cognitive functioning right now?*) on an 11-point Likert scale ranging from 0=*bad: my thinking is very difficult or slow* to 10=*good: my thinking is sharp and quick* [162,163]. Participants may opt out of messages for the daily surveys and switch to a paper-and-pencil log.

##### Randomization

One week before the first session of MHB or the HEP, the RA randomizes participants to receive either 8 weeks of the MHB intervention or the HEP education control. Randomization follows a 1:1 ratio using permuted blocks of size 4. To maintain blinding of group assignments, participants are informed that they can participate in 1 of 2 programs: MHB 1 (active intervention [MHB]) or MHB 2 (control [HEP]). To reduce contamination, we ask participants not to share specific information discussed in the group (eg, skills learned and topics discussed) with anyone for the duration of the study. All participants will receive both electronic and paper copies of their assigned treatment manual.

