### Ethical Considerations

The Mass General Brigham (MGB) institutional review board (IRB) approved all study procedures (2023P001770). All participants review and sign written informed consent with a clinical research assistant (RA) before completing study procedures. Consent informs participants that, with any group-based intervention, there may be confidentiality and privacy risks. To minimize these risks, we discuss the importance of confidentiality at the start of each group; request that participants attend the session from a private location; and all data are deidentified, maintained in a secured location, and only accessed by IRB-approved members of the research team. Participants are compensated up to US $220: US $30 for before the intervention assessments, US $60 for after the intervention assessments, US $90 for 6-month follow-up assessments, with an additional US $40 for 7 out of 7 valid days of Garmin Vivosmart 5 wear during the before the intervention assessment period. This compensation strategy is meant to optimize participant engagement and motivation for 6-month follow-up assessments.

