### Screening and Enrollment

The RA logs all referral information in a standardized REDCap (Research Electronic Data Capture; Vanderbilt University) [105] database. Participants have the option to complete an initial screening survey independently or by telephone with the RA. The RA contacts all potentially eligible participants to answer questions about the study, collect availability for groups, and assess technology access and readiness. Individuals who do not meet study criteria are offered resource sheets developed for older adults with SCD. The principal investigator ([name]) reviews all eligibility decisions and consults with the multidisciplinary study team if needed. After group times have been set, the RA meets with participants individually over Zoom to schedule the before the intervention assessments, review study technology, and obtain electronic informed consent via REDCap. The RA uses secure email to send confirmation and Zoom links for the before the intervention assessments.

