### Assessments

#### Overview

Tables 1 and 2 detail the assessments and the frequency of data collection. All assessment data are stored in a REDCap database. An RA blinded to randomization reviews all measures for missing data, errors, or invalid responses.

**Table 1 table1:** Primary outcomes.

Construct and measure			Scoring		Criteria		Time point

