#### Garmin Vivosmart 5 Watch

We selected the Garmin Vivosmart 5 to replace the ActiGraph GT9X. Our preliminary studies revealed that the ActiGraph GT9X is cost prohibitive and frequently had technical support issues that resulted in interrupted data collection and study operations. Additional participant and scientific advantages of the Garmin Vivosmart 5 include (1) its commercial availability and user-friendly design, which promote future scalability; (2) the ability to conduct blinded assessments at study end points by selecting watch faces that do not display step count data; and (3) its reliability and validity for passive monitoring of physical activity and sleep among older adults [170-174]. Our testing showed that step counts measured using the Garmin Vivosmart 5 were internally consistent and produced similar estimates to another widely used device (Fitbit).

The Garmin Vivosmart 5 serves 2 purposes in the RCT. First, in conjunction with the Garmin Connect app, it provides self-monitoring tools (eg, real-time step counting and “move” notifications) to promote engagement in physical activity and sleep [171]. Second, it provides objective, continuous, and passive data to capture within-person changes [175,176] in these lifestyle behaviors during the intervention [177,178]. Wearable devices are both feasible and acceptable for older adults and provide valid measurements of physical activity and sleep [179].

The Garmin Vivosmart 5 is mailed to participants 1 to 2 weeks before the intervention phase, and they set up the watch with the RA during an individual Zoom session. The RA pairs the watch with the participant’s mobile phone and reviews basic instructions (how to wear, charge, and sync). Participants are instructed to wear the Garmin Vivosmart 5 on their nondominant hand for 24 hours per day (except when briefly removing it for charging) to track steps and sleep. The watch is waterproof and can last up to 7 days per charge. Participants sync their data using the Garmin Connect app daily and charge the watch regularly. The RA turns off self-monitoring features (step count and sleep notifications) for blinded before the intervention assessments in both MHB and HEP groups. After the before the intervention assessments are complete, the RA turns on the self-monitoring features in the MHB group only because activity reinforcement is a core component of the technology-enhanced intervention.

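### A single published block size of 4, run by an RA role that knows participants and past arms, makes about 32% of allocations certain beforehand if the RA can choose the order of entry

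*Protocol article*

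**What the plan says.** The Randomization section fixes the method: "Randomization follows a 1:1 ratio using permuted blocks of size 4". It also names who allocates and when: "One week before the first session of MHB or the HEP, the RA randomizes participants".

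The same role label appears wherever staff meet participants. Under Screening and Enrollment the RA logs referrals, contacts potentially eligible people, checks technology readiness and meets each person to "review study technology, and obtain electronic informed consent via REDCap". Under Garmin Vivosmart 5 Watch the RA sets up the watch and monitors wear. After the baseline assessments, "the RA turns on the self-monitoring features in the MHB group only", so the role learns each person's arm.

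The Assessments overview also has a blinded staff member: "An RA blinded to randomization reviews all measures for missing data, errors, or invalid responses". More than one RA is therefore implied.

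The Results overview reports 21 randomized (11 MHB, 10 HEP) in cohorts of 9 and 12 as of June 1, 2024, with 17 eligible people on hold and enrollment planned to finish by December 2024.

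**The concern.** With one known block size, anyone who knows the earlier allocations and where the blocks begin can work out some of the later ones. Here the role that allocates also knows the participants. The watch arrives 1 to 2 weeks before the intervention phase and randomization comes one week before the first session, so some baseline wear may already be visible. If that person also decides who is entered next, a keen participant can be matched to a known slot, without any deliberate intent.

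This bears on the primary outcomes. Several Table 1 benchmarks (watch wear, daily surveys, attendance, satisfaction) depend on motivation, and Primary Analyses (Feasibility) reports them separately by arm against Go–No-Go thresholds. The Discussion calls the trial a dress rehearsal for the efficacy trial, so the procedure may be carried forward.

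**Working it through.** The article states no predictability figure, so there is none to reproduce.

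**Inputs from the article.** Blocks of 4, 1:1 (Randomization); 50 participants (Objectives); 21 already randomized, in cohorts of 9 and 12 (Results, Overview).

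**Assumptions not in the article.** Allocations are released one at a time; the observer knows all earlier allocations and the block boundaries; 25 participants per arm.

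**Certain allocations per block.** A 1:1 block of 4 has 6 possible sequences. A slot is certain once one arm has its two places filled.
- Slots 1 and 2: probability 0.
- Slot 3: the first two are alike in 2 of 6 sequences, so 1/3.
- Slot 4: probability 1.
- Expected number per block: 0 + 0 + 1/3 + 1 = 4/3, and (4/3)/4 = 33.3%.

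**Over 50 participants.** 50 = 12 full blocks + 2 slots. 12 × 4/3 + 0 = 16, and 16/50 = 32%.

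**Already allocated.** 21 = 5 full blocks + 1 slot. 5 × 4/3 = 6.67. Restarting per cohort gives the same: 9 yields 2 × 4/3 = 2.67 and 12 yields 3 × 4/3 = 4, total 6.67.

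**Remaining 29, if blocks run on.** 16 − 6.67 = 9.33. Directly: the rest of block 6 gives 0 + 1/3 + 1 = 1.33, six full blocks give 8, and the last two slots give 0. If blocks restart per cohort, the figure depends on future cohort sizes, which are not stated.

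**Knowable when consent is taken.** Only the remainder of a block left open by the previous cohort can be known then. With 0, 1, 2 or 3 slots of that block used, the expected number is 0, 0, 2/6 × 2 = 0.67, or 1. After cohort 1 (9 = 2 blocks + 1) it is 0. After 21 it is 0 again.

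**Effect of one swap.** With arm sizes fixed, steering exchanges two people. If one meets a benchmark and the other does not, each arm's rate moves by 1/25 = 4 percentage points, in opposite directions. If both or neither meet it, the shift is 0. At the 70% threshold, 17/25 = 68% and 18/25 = 72%, so one swap matters only for an arm already at the edge.

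**Alternatives.** These were simulated for 50 participants, with sizes drawn at random with equal probability and an observer who knows the set of sizes and all earlier allocations:

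| Block sizes | Certain allocations | Best-guess accuracy | Largest running imbalance |
|---|---|---|---|
| 4 only | 32% | 70% | 2 |
| 2 and 4 | 11% | 72% | 2 |
| 4 and 6 | 6% | 69% | 3 |

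Varying the size removes most of the certainty but hardly changes how well an informed observer can guess. A fixed entry order is therefore the more important half of the remedy.

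**The case against.** The strongest reply is that consent comes first. Group times are set, participants consent, and the cohort is randomized later, so almost nothing is knowable at consent. This stands. A reader might infer that the RA could decide whom to enroll from knowledge of the next slot; the sequence of steps in the article largely rules that out.

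The reply also notes that the article is silent on how the list is generated, stored and released and on who sets the order of entry, and that an article commonly leaves such detail to the full protocol. This stands too. If a cohort's list is released as a batch against a fixed order, no allocation can be used stepwise. Nor is it established that one person does everything, given the blinded RA. Publication adds little, because staff would know the block size anyway.

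The consequence is modest. Primary results are proportions by arm against fixed thresholds, with no between-arm test described, and recruitment and protocol-deviation benchmarks cannot be steered. Attendance has shown almost no variation so far: 9 of 9 in cohort 1 reached at least 6 sessions, and cohort 2 was at 100% after 5 sessions.

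What remains is that the block size is stated, not left open. Unstated detail in a full protocol could conceal the list, but it could not vary the size without contradicting the article.

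**Conclusion.** The point holds as a low-priority improvement to a stated design choice. About 32% of allocations (16 of 50, and about 9 of the remaining 29 if blocks run on) are certain beforehand, on three conditions: stepwise release, knowledge of past arms and block boundaries, and discretion over the order of entry or over deferral to a later cohort. The article supports knowledge of past arms for the RA role. It neither states nor excludes stepwise release or discretion over entry.

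Two stronger readings should be resisted. One is that a third of allocations are in fact open to manipulation; that treats the conditions as established. The other is that the 11 to 10 split or the high adherence so far points to steering. The split is what blocks of 4 would give, and nothing in the article suggests that participants were steered.

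**What to change.** For participants not yet randomized:

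1. Enter each cohort's consented participants in an order fixed beforehand, such as ascending study ID, so that nobody chooses who takes the next slot.
2. Replace the single size with randomly varied block sizes. Sizes 2 and 4 keep the running difference between arms to at most 2, as blocks of 4 do now, and cut certain allocations from 32% to about 11%.
3. Generate the list in a locked REDCap randomization module not visible to staff with participant contact.

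If the full protocol already provides the first and third items, the article needs only a sentence saying so.

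The cost is a new list and one or two sentences in the protocol; REDCap is already in use. Larger blocks such as 6 lower the certain share further (about 6% with sizes 4 and 6) but could leave a difference of up to 3 in a small cohort, which matters when MHB groups are meant to hold 5 to 10 people. These limits on imbalance apply to the running total, or to a cohort when the list restarts with it.

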### Treatment Arms

#### MHB Intervention

The iterative development of MHB has followed the NIH Stage Model [62] and Science of Behavior Change [190] frameworks. The objective of MHB is to increase the uptake and maintenance of lifestyle behavior modification to reduce the risk of AD/ADRD and cognitive decline among older adults, fostering long-term brain health and well-being (Figure 3). This objective aligns with the Scaffolding Theory of Aging and Cognition [191], which posits that lifestyle behaviors enhance “neural compensatory scaffolding,” thereby preserving brain structure, function, and cognition with aging. MHB targets *modifiable* lifestyle behaviors identified in our meta-analysis [63], relevant literature on modifiable AD/ADRD risk factors [22,192,193], and similar multidomain lifestyle interventions [30,31]. Modifiable lifestyle behaviors include physical activity, adherence to a Mediterranean diet, sleep quality, alcohol use, tobacco cessation, social functioning, and mental activity. MHB does not target other AD/ADRD risk factors that are not modifiable through a group-based behavioral intervention (eg, a history of head injury or exposure to air pollution [22]).

The intervention design and procedures were informed by MHB preliminary studies [64-66] and a similar virtual program for older adults with early cognitive decline [74,81,83,92,194]. MHB is delivered via 90-minute Zoom meetings in small groups of 5 to 10 older adults with early AD/ADRD risk (refer to Textbox 1 for the eligibility criteria). The MHB program is led by a clinical health psychologist with aging expertise and a supervised clinical psychology doctoral trainee. All sessions provide education on AD/ADRD risk factors and teach evidence-based behavior modification skills grounded in cognitive behavioral therapy [195] and mindful self-regulation theory [38-40]. Guided by qualitative work with older adults [71,96], we adapted all program skills to account for challenges related to SCD symptoms and aging (eg, forgetfulness, mobility issues, and loneliness). Textbox 2 contains a full list of topics for each MHB session. Participants receive a copy of the manual along with access to the program website, which includes educational videos, recordings of mindfulness skills, and additional resources.

In the first session, the group leader provides an overview of the program, sets expectations for participation (eg, attendance, home practice, and appropriate group behavior), defines key terms (eg, dementia, brain health, and mindfulness), and allows group members to introduce themselves. The remainder of the first session and all subsequent sessions follow the same agenda: review previous material (10% of session time), problem-solve adherence barriers (10%), discuss progress toward participants’ goals (10%), provide education on AD/ADRD risk factors (30%), and practice and apply behavior modification and mindfulness skills (40%). Group members are encouraged to collaboratively support each other by sharing strategies for coping with SCD symptoms and achieving lifestyle goals. MHB group participants wear the Garmin Vivosmart 5 to increase their daily step count gradually and safely following a quota-based pacing protocol (10% increase each week if step goal is achieved) [83]. At the end of each session, participants set an individualized specific, measurable, achievable, relevant, and timely (SMART) lifestyle behavioral goal [196]. During the week between MHB sessions, participants execute their SMART goal and practice mindfulness (5-10 min/d).

**Figure 3 figure3:**
[figure not shown]
Conceptual model of My Healthy Brain (MHB). AD/ADRD: Alzheimer disease and Alzheimer disease–related dementias.

Session outline for My Healthy Brain (MHB) and the health enhancement program (HEP).
**MHB sessions and content**
Session 1: Brain health and mindfulnessEducation: define brain health, bust common myths about brain health, identify protective lifestyle factors, and understand the benefits of mindfulnessMindfulness: practice “mindful awareness of breath” meditationBehavioral: reflect on motivations for participating, assess current brain health habits, and set lifestyle goals for the programSession 2: Physical activity and walkingEducation: understand the importance of physical activity (walking) for brain health, and use a wearable device (Garmin Vivosmart 5 watch) to monitor and reinforce my daily step countMindfulness: pay attention nonjudgmentally by practicing “body scan” meditationBehavioral: set realistic and achievable walking goals (quota-based pacing), and link activities to enjoyment and purposeSession 3: Quality sleepEducation: understand the importance of sleep for brain health, and use a wearable device (Garmin Vivosmart 5 watch) to monitor sleep (total time and efficiency)Mindfulness: learn how mindful responding can lead to healthier lifestyle choices through the “mindful STOP (stop, take a breath, observe, and proceed)” meditationBehavioral: use behavioral sleep hygiene strategies and problem-solve barriers to getting quality sleepSession 4: Mediterranean and Mediterranean–Dietary Approaches to Stop Hypertension Intervention for Neurodegenerative Delay (MIND) dietEducation: understand the importance of the Mediterranean or MIND diet for brain healthMindfulness: bring mindfulness to my daily experiences through “mindful eating” meditationBehavioral: notice hunger and fullness urges to reduce overeating, and track dietary changes using a MIND diet logSession 5: Mental activity and cognitive reserveEducation: understand the importance of being mentally active for brain health, and identify cognitive strengths and weaknessesMindfulness: learn the brain health benefits of mindfulness and practice “bringing awareness to unwanted experiences” meditationBehavioral: develop compensatory strategies for memory-related problems (MRPs), and get mentally active to build cognitive reserveSession 6: Social activity and brain healthEducation: understand the importance of social activities for brain health and the risks of lonelinessMindfulness: practice mindful communication to improve my relationships, openness, and compassion to myself and others; and practice “love and kindness” meditationBehavioral: brainstorm ways to become more socially active, and create shared activity plans to reduce lonelinessSession 7: Mindfulness of unhealthy urgesEducation: understand the impacts of alcohol, tobacco, and substance use on brain health, identify urges that become unhealthy habitsMindfulness: practice tolerating urges with the “urge surfing” meditationBehavioral: break unhealthy habits by identifying environments and stressors that derail lifestyle goalsSession 8: Maintaining a brain-healthy lifeEducation: understand how to sustain a healthy lifestyle and prepare for the end of MHBMindfulness: review how to integrate mindfulness into daily life and practice “mountain” meditationBehavioral: evaluate progress in the program and develop a plan to main acquired skills
**HEP sessions and content**
Session 1: Program overview and MRPsProgram goals, understand MRPs, how stress and MRPs are connected, and the impact of stressSession 2: The connection between MRPs and physical wellnessUnderstand the connection between MRPs and physical wellnessSession 3: Sleep and wellness—connection with MRPsHealthy sleeping strategies and cognitive and physical healthSession 4: Exercise and wellness—connection with MRPsPhysical exercise, maintaining healthy weight, and tips for getting activeSession 5: Nutrition—connection with MRPsBasic nutrition, unique needs and tips for older adults, and portion sizeSession 6: Substance use, supplements, and medications—connection with MRPsThe impact of tobacco and alcohol use on brain health and aging, guidance on over-the-counter memory supplements, and medication managementSession 7: Social support and loneliness—connection with MRPsThe impact of social isolation on brain health, types of social support, and physician supportSession 8: Program reviewOverview of program content

